**Phase 2**

While not a clinical trial (since all patients will be offered usual care), Aim 3 will include a prospective evaluation of whether receiving proactive intervention by the Hypoglycemia Champion (augmented care delivered by an APM trained in the new standard of care) is associated with better diabetes regimen safety among KPNC members at high risk of hypoglycemia compared to usual care (usual care). All KPNC patients at high risk for hypoglycemia are expected to receive the new HOAP protocol delivered by their usual APM. Outcomes among study participants in Aim 3 will compared to data-only patients receiving usual care.

Describe whether the study involves educational tests, survey procedures, or interview procedures.

N/A

Describe whether the research involves benign behavioral interventions on adult subjects. Note: Benign behavioral interventions are brief in duration, harmless, painless, not physically invasive, not likely to have a significant adverse lasting impact on the subjects, and not offensive or embarrassing to the subjects. Examples include having subjects play online games or solving puzzles under various noise conditions.

N/A

If the study involves either educational tests, survey procedures, interview procedures, or benign behavioral interventions (on adults), specify whether one of the following criteria is met:

- (i) The information obtained is recorded by the investigator in such a manner that the identity of the human subjects cannot readily be ascertained, directly or through identifiers linked to the subjects

N/A

- (ii) Any disclosure of the human subjects' responses outside the research would not reasonably place the subjects at risk of criminal or civil liability or be damaging to the subjects' financial standing, employability, educational advancement, or reputation

N/A

- (iii) The information obtained is recorded by the investigator in such a manner that the identity of the human subjects can readily be ascertained, directly or through identifiers linked to the subjects, and an IRB conducts a limited IRB review to make the determination

N/A

**5. Study Population****a. Number of Subjects**

State the number of subjects you plan to include at the KP region to which this study is being submitted. If applicable, distinguish between the number of subjects who are expected to be enrolled/screened and the number of subjects needed to complete the research procedures (e.g. number of subjects excluding screen failures).

**Phase 1**

Aim 1 meeting participants are not research subjects. They are collaborators with subject matter expertise. Aim 2 is an activity with no research subjects.

**Phase 2 )**

Aim 3 will identify 200 eligible patients receiving usual care from KPNC; half of these will be randomly allocated to receive augmented usual care (i.e., additional oversight by a Hypoglycemia Champion APM).

As appropriate, differentiate between different populations of subjects within the same study (e.g. subject/caregiver, parent/child, patient/physician).

In this study, the only research subjects are study participants in Aim 3 receiving augmented usual care from the HC APM.

If this is a multicenter study, indicate the total number of subjects to be accrued across all sites.

N/A

If this study has a data only component, indicate the total number of patient records to be accessed. Control subjects for Aim 3 will have 100 matched subjects for data-only.

**b. Inclusion and Exclusion Criteria**

- Describe the criteria that define who will be included or excluded in your final study sample.

**Phase 2**

Eligibility criteria for Aim 3 (study participants and data-only patients) will include patients with type 2 diabetes (T2D) at high risk for hypoglycemia, including those 1) designated as “high-risk” by the existing hypoglycemia risk stratification tool[1, 2] developed by the investigator team and currently implemented into Health Connect, or 2) who have had an ED visit or hospitalization for hypoglycemia (as primary or principal diagnosis, respectively) in 6 months prior to cohort baseline (date of enrollment in cohort).

No exclusion criteria.

- Describe how individuals will be screened for eligibility.

**Phase 2**

The data analyst will identify a cohort of 200 eligible patients from the KPNC Diabetes Registry based on the inclusion and exclusion criteria. 100 study participants will be randomly allocated to receive augmented usual care; the remaining 100 data-only patients will be selected for comparison. No screening is needed.

- If you are planning to conduct remote informed consent, how will you assure that participants should not be excluded from the study? e.g. how will you determine that potential participants can understand, adequately hear, have appropriate decision making capacity, and have a copy of the informed consent form?

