patient's problem list, HbA1c<8% (HEDIS-defined glycemic control metric), and ED visits or hospitalizations for hypoglycemia based on primary diagnosis. The study hypothesis is that study participants will have more glucagon prescribing, CGM use, and inclusion of hypoglycemia on the problem list, with stable glycemic control (HbA1c<8%), and fewer ED visits or hospitalizations for hypoglycemia. The investigators will also conduct Heterogeneity of Treatment Effect (HTE) analyses by age (<75 vs. ≥ 75 years), enrollment criterion (hypoglycemia prediction algorithm vs ED/hospital hypoglycemia admission), and race/ethnicity.

Assess whether this study involves a clinical trial. Clinical trial means a research study in which one or more human subjects are prospectively assigned to one or more interventions (which may include placebo or other control) to evaluate the effects of the interventions on biomedical or behavioral health-related outcomes.

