- If assent will only be obtained from some children (because of very young age, severe cognitive impairment, etc.), indicate which children will be required to assent and which will not.

N/A

- When assent of children is obtained, describe whether and how it will be documented.

N/A

- When subjects might reach the age of majority during the study, describe the plan to obtain consent from these subjects at that time using an adult consent form.

N/A

g. Secondary Research for Which Consent is Not Required:

Note: Research involving the use of identifiable biospecimens does not apply to this section.

Note: Although consent may not be required, justification for a waiver of HIPAA Privacy Authorization may still be required.

Secondary Research of identifiable private information or identifiable biospecimens may not require informed consent if at least one of the criteria listed below is met. Select at least one of the following criteria and provide a rationale for how the criteria is met:

- Use of publicly available identifiable private information or identifiable biospecimens.

N/A

- The information and/or biospecimens are recorded by the investigator in such a way that the identity of the subjects cannot be readily ascertained, and the investigator will neither contact the subjects nor re-identify subjects.

N/A

- The research involves only information collection (i.e., no biospecimen collection) and the analysis of this identifiable health information is regulated by HIPAA.

Data will be collected on data-only matched controls (receiving usual care subsequent to the regionwide dissemination of HOAP).

**8. HIPAA Privacy Rule Authorization**a. Written HIPAA Privacy Rule Authorization:

Describe the plan to obtain a signed Privacy Rule Authorization from each subject.

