**Aim 2**

Months 2-4: Workflow/clinical pathway will be developed by PIs.

**Phase 2**Aim 3

Months 5-6:

- Develop procedures and metrics for outcome evaluation
- Identify eligible patients (N=200)(have a high hypoglycemia risk score or a recent ED visit or hospitalization for hypoglycemia); randomly select study participants and data-only patients (matched sample)
- Collect baseline EMR data on study participants and data-only patients

Months 7-12:

- HC APM conducts outreach to study participants for assessment and evaluation; provides hypoglycemia intervention to study participants.

Months 13-21

- Collect outcome data from EMR for study participants and data-only patients.

Months 21-24

- Analyze data and draft manuscript

- Procedures to monitor subjects for safety, including who will review the data and at what frequency for safety issues.

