**Phase 2**

Power Calculation: In preparation for this proposal, baseline use of hypoglycemia-prone medications (e.g., sulfonylureas, mealtime, or mixed insulin) was evaluated in 3921 KPNC patients identified as “high risk” by the KPNC hypoglycemia risk tool. Among these patients, 75% were on hypoglycemia-prone treatment. Approximately 60% of the intervention arm and 20% of the usual care arm will be prescribed safer diabetes regimens within 6 months compared

to baseline. The minimum number of subjects needed to detect this 40% absolute difference, assuming 90% power and a 10% attrition rate, is 86 patients (43 per arm). With an enrollment size of 200 (100 per arm), this trial is more than adequately powered to detect the hypothesized difference.

- Any procedures that will be used for quality control of collected data.

Data analysts routinely inspect the data for corrupt fields or extreme outliers.

c. Sharing of Results with Subjects

Describe whether results (study results or individual subject results, such as results of standard or research lab tests and genetic tests) will be shared with subjects or their providers and under which circumstances.

N/A

If the study carries a risk of incidental findings, describe your plan for evaluating these and determining whether and how subjects or their providers will be given this information.

N/A

If laboratory results will be shared with subjects or their healthcare providers, verify that the laboratory conducting the test is Clinical Laboratory Improvement Amendments (CLIA) certified.

N/A

Describe how study participants will be updated on research progress via newsletter, summary, etc. Consider incorporating such updates to study participants as part of ongoing retention efforts.

N/A

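### The comparison is called both randomised and matched, no balancing factor is named, and the primary analysis ignores baseline listed-drug use, which decides who can have the outcome

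*Supplement*

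**What the plan says.** All references are to the protocol version dated January 27, 2025.

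- **Random allocation.** Section 5b: "The data analyst will identify a cohort of 200 eligible patients from the KPNC Diabetes Registry based on the inclusion and exclusion criteria", and then "100 study participants will be randomly allocated to receive augmented usual care; the remaining 100 data-only patients will be selected for comparison". Section 5a also says that half of the 200 are randomly allocated.
- **Matching.** Section 5a adds: "Control subjects for Aim 3 will have 100 matched subjects for data-only". Section 7g: "Data will be collected on data-only matched controls (receiving usual care subsequent to the regionwide dissemination of HOAP". The section 9a timeline puts both ideas in one line for Months 5-6: "randomly select study participants and data-only patients (matched sample". No matching variable is given.
- **Timing.** The same Months 5-6 entry includes "Identify eligible patients (N=200)(have a high hypoglycemia risk score or a recent ED visit or hospitalization for hypoglycemia" and the baseline EMR pull. Outreach follows in Months 7-12.
- **Outcome and eligibility.** The primary outcome (section 4) is discontinuation at 6 months of sulfonylureas, mealtime insulin or mixed insulin. Section 5b does not require use of any of these and states no exclusions. The power paragraph in section 9b reports, for patients flagged by the risk tool: "Among these patients, 75% were on hypoglycemia-prone treatment".
- **Subgroups.** Section 4 names age and "enrollment criterion (hypoglycemia prediction algorithm vs ED/hospital hypoglycemia admission), and race/ethnicity" for treatment-effect heterogeneity. Section 9b calls these analyses exploratory.
- **Analysis.** Section 9b gives an intent-to-treat chi-square test and binomial regression, with no covariate, stratum or pair term.

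**The concern.** Baseline drug use is an unusually strong prognostic factor here, because a patient on none of the listed drugs has nothing to discontinue. If about a quarter of each arm cannot have the event, a chance difference between arms in that quarter passes directly into the primary difference. The information sits in the EMR before outreach starts, so using it needs no further data.

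The allocation text adds a second difficulty. A matched sample without matching variables cannot be carried out or checked. If the controls are simply the remaining 100 of a cohort of 200, there is no pool left to match from, unless pairs are formed first and randomised within pair. The plan does not describe that. Whichever scheme is meant, the analysis does not reflect it.

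At stake are the precision of the primary estimate and the face validity of the baseline table. The validity of the test is not in question.

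**Working it through.** **Inputs.** Cohort 200, allocated 100:100 (sections 5a, 5b). User share 75%, so 150 users and 50 non-users (section 9b, assumed to carry over to the trial cohort). Rates of 60% vs 20% (section 9b). Non-users are assumed to have no events and to stay in the denominator.

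**The plan's own figures.** The plan gives no figure for imbalance or for adjusted precision. Its one derived figure is 43 per arm for 60% vs 20% at 90% power with 10% attrition. At two-sided 0.05 (assumed; alpha is not stated) I get 30/0.9 → 34 per arm, or 35/0.9 → 39 with continuity correction. The plan's 43 is larger than needed, and nothing below depends on it.

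**1. Chance imbalance under plain allocation.** Let X be the number of users in the intervention arm, hypergeometric (200, 150, 100).

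- Var(X) = 100 × 0.75 × 0.25 × (100/199) = 9.42, SD 3.07.
- Gap in user share = (2X − 150)/100, SD = 2 × 3.07 = 6.1 points.
- Exact tails: P(gap ≥ 8 points) = 25%, P(≥ 10) = 14%, P(≥ 20) = 0.2%.

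**2. Effect of a 10-point gap (80 vs 70 users) on the expected primary difference.**

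- Reading A, 60% vs 20% as whole-arm rates: rates among users are 0.60/0.75 = 80% and 0.20/0.75 = 26.7%. Difference = (80 × 0.80 − 70 × 0.267)/100 = 45.3 points, against 40 when balanced.
- Reading B, 60% vs 20% among users only: (80 × 0.60 − 70 × 0.20)/100 = 34 points, against 30 when balanced.
- No effect, 20% among users in both arms: (16 − 14)/100 = 2 points, against 0.

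**3. Variance of the primary difference, 150 users held fixed.** For user rates p1 and p0:

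- Within strata: 75 × [p1(1 − p1) + p0(1 − p0)]/100².
- Added by chance imbalance: 9.42 × (p1 + p0)²/100².

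| | Within | Imbalance | SE plain, unadjusted | SE with imbalance removed | Variance cut |
|---|---|---|---|---|---|
| A (80% vs 26.7%) | 0.002667 | 0.001072 | 6.1 points | 5.2 points | 0.001072/0.003739 = 29% |
| B (60% vs 20%) | 0.003000 | 0.000603 | 6.0 points | 5.5 points | 0.000603/0.003603 = 17% |

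**4. Which step brings the gain?** Analyse plain allocation as 0.75 × (difference among users). Its variance is the within-strata term times about 1 + 9.42/75² = 1.0017. Under reading A the SE is 5.17 points, against √0.002667 = 5.16 with perfectly balanced allocation. Adjustment therefore brings essentially all of the gain.

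**5. Test properties (simulation, 200,000 runs per case, rates among users).**

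| | Plain, unadjusted | Stratified, unadjusted | Plain, analysed within users |
|---|---|---|---|
| Type I error, 20% vs 20% | 0.051 | 0.045 | 0.049 |
| Power, 40% vs 20% | 0.73 | 0.74 | 0.77 |
| Power, 60% vs 20% | 0.998 | 0.999 | 0.999 |

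Stratifying the allocation without adjusting leaves the chi-square test slightly conservative, which is a further reason to put the factor in the analysis.

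**The case against.** The strongest reply is that simple randomisation of 200 patients is valid and the effect on inference is small. That stands. Type I error is about 0.05 either way, power at the planned rates is above 0.99, and chance imbalance does not bias a randomised comparison.

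A reader might infer that the allocation is definitely unstratified. The documents do not support that. Three places call the controls matched, and if pairs were formed on drug use and randomised within pair, the imbalance above would not arise. What can be said is that no factor is specified.

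A reader might also infer one batch allocation with no enrollment over time. Sections 5b and 9a read that way. However, section 5b sets baseline at each patient's date of enrollment, section 6 has the Hypoglycemia Champion enrolling participants, and section 9a runs enrollment to 01/31/2026. The remedy does not depend on which is right, because the records exist at each patient's entry.

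A variance cut of one third is tempting too: (0.2 × 0.8 + 0.6 × 0.4)/100 = 0.0040 against 0.002667. That formula treats the number of users as random, whereas in an identified cohort it is fixed, which gives 29% at most on the plan's rates.

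Balance in the planned subgroups is a weak argument. The share entering by ED or hospital event is not given. If it were 20 of 200 (assumed), a 13:7 or worse split has a 24% chance, but 13:7 raises the SE of that stratum's contrast by only √[(1/13 + 1/7)/(1/10 + 1/10)] − 1 = 4.8%, at equal outcome variance.

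Finally, the allocation may already be done, given the version date and the Months 5-6 entry, though the documents do not confirm it. That limits the allocation change and leaves the analysis change open.

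**Conclusion.** The point holds as a low-cost improvement. The plan describes the comparison as random and as matched, specifies neither beyond the 1:1 ratio, and leaves out of the analysis a factor that fixes in advance who can have the primary event. Adjusting for it would cut the variance of the primary difference by about 17% to 29%, depending on whether 60% vs 20% refers to users or to whole arms. It would also remove the influence of a user-share gap that has a 14% chance of reaching 10 points under plain allocation.

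The documents do not support a conclusion that the primary test is biased or underpowered.

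The figures assume 75% users in the trial cohort, although that percentage comes from patients flagged by the risk tool and eligibility also admits patients after an ED visit or hospitalization. They also assume no events in non-users, with non-users kept in the denominator. The gain shrinks as the user share approaches 100%.

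**What to change.** 1. **Section 9b.** Make the primary estimate a risk difference from the binomial regression, standardised over baseline listed-drug use (user or non-user) with weights from the whole cohort. Non-users have a difference of zero by construction, so avoid a model that forces one common risk difference across strata, and avoid inverse-variance weights. The unadjusted chi-square test can stay as a supporting analysis.
2. **Sections 5b and 9a, if allocation is not yet done.** Allocate 1:1 within strata of baseline listed-drug use and enrollment criterion. Stop at these two factors to avoid sparse cells.
3. **Sections 5a, 7g and 9a.** Align the matching language with the scheme actually used. If pairs were formed, name the variables and reflect the pairing in the analysis. If not, drop the word.

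The cost is a few sentences in the protocol and a few lines of code, with no added patients or data. If allocation is already done, item 1 alone recovers essentially all of the precision gain. It should be fixed before outcome data are examined.

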**Phase 2**

A waiver of informed consent is requested.

- If information or biospecimens will be obtained for the purpose of screening, recruiting, or determining eligibility, informed consent is not required if one of the following criteria is met. Select one of the following criteria and provide a brief explain for how the criteria is met.
  - ☒ The investigator will obtain information through oral or written communication with the prospective subject or legally authorized representative, or
  - ☐ The investigator will obtain identifiable private information or identifiable biospecimens by accessing records or stored identifiable biospecimens

N/A

**IMPORTANT NOTES:** Although informed consent may not be required, HIPAA Privacy Authorization may still be required. Also, if this study is FDA-regulated, then consent may be required.

- Describe the plan for disposition of information/biospecimens collected during recruitment/screening in the event of a screen failure or when a potential subject is contacted but declines participation (e.g., destroyed immediately, destroyed at end of study, retained for separate analysis or so that subjects are not contacted repeatedly about participation after they have declined, etc.).

N/A

**c. Subjects Vulnerable to Coercion or Undue Influence**

Indicate whether you will include or exclude each of the following special populations. Justify the inclusion of any of these populations. Describe additional safeguards to protect the rights and welfare of these subjects. Note: This refers to subjects who are known members of these populations upon enrollment or at any time during the study.

- Children

Study will not include children.

- Neonates of uncertain viability or nonviable neonates (up to 28 days post birth)

N/A

- Prisoners (NOTE: The KP IRB does not have the appropriate membership to review research involving prisoners. Consultation with the IRB Office will be required.)

IMPORTANT NOTE: Consider whether subjects will be in a vulnerable category at the time of information/biospecimen collection or during analysis. For instance, if you collect information/biospecimens about children who were ages 12 – 15 from years 2000 – 2002, you know that now those individuals are no longer children.

#### Individuals with Impaired Decision-Making Capacity

Indicate how you will assess decision making capacity and cognitive function. This process must be tailored based on the risk and design of the study.

#### **Phase 2**

Decision-making capacity or cognitive function of participants will not be assessed.

State whether individuals with impaired decision-making capacity will be included.

N/A

Explain the extent of cognitive impairment (complete, fluctuating, progressive, or temporary).

N/A

Justify their inclusion and explain any protections to mitigate risk (such as the involvement of a caregiver or legally authorized representative).

N/A

Describe the process to determine whether an individual is capable of consent, and submit any documents that will be used assess decisional capacity.

N/A

List the individuals from whom permission will be obtained in order of priority. (E.g., durable power of attorney for health care, court appointed guardian for health care decisions, spouse, and adult child.

N/A

Describe the process for assent of the subjects by addressing the following:

- Whether assent will be required of all, some, or none of the subjects. If assent will be obtained from some subjects, indicate which subjects will be required to assent and which will not.

N/A

- If assent will not be obtained from some or all subjects, an explanation of why not.

N/A

- When assent is obtained, describe how it will be documented.

N/A

HIV Status: N/A

If the study will be ascertaining subject HIV status for study exclusion/inclusion, please indicate how:

- ☐ Prospective laboratory HIV testing of subjects for the study
- ☐ Surveying subjects about their HIV status
- ☐ KPNC HIV Registry access or existing electronic health record data\*

\*If you checked this option, you must first gain approval from the HIV Steering Committee by contacting [name], MPH. The HIV Steering Committee approval must be submitted to IRBNet.

Will TPMG physicians be directly contacted to enroll as study participants? ☐ Yes ☒ No

**If “yes” the contact must be approved by [name] [name], Associate Executive Director, TPMG, prior to IRB review. [name] approval must be submitted to IRBNet.**

Other Populations Targeted for Recruitment

If you are targeting a population that may be vulnerable to coercion or undue influence based on the specific circumstances of the study, describe how you will ensure that participation is voluntary and minimize any added risk. (Common examples include employees, students, economically or educationally disadvantaged persons, etc.)

N/A

d. Setting

Describe the sites or locations where your research team will conduct the research.

